### Additional analyses

If the analyses are adjusted for missingness, we will also perform a complete case analysis by excluding subjects with missing values from the analysis to understand the sensitivity of the conclusions to missing data. We will also undertake a prior sensitivity analysis for the primary analysis using a minimally informative prior for the treatment effect.

### Heterogeneity of treatment effects analysis

Due to the heterogeneity of bronchiolitis, we will also perform a heterogeneity of treatment effect analysis using a predictive approach [30, 31]. We will use a risk modelling approach by developing a multivariable risk model adjusted for, at a minimum, age, sex, prematurity, length of illness at time of enrolment, history of previous wheezing, personal history of eczema, family history of atopy, household smoke exposure, prenatal smoke exposure, breastfeeding and virus type [32, 33] but ignoring treatment assignment. We will create ten risk strata based on this model and report the median treatment effect with 95% credible intervals within each strata using Bayesian risk regression.

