## Method/Design

### Design and setting

The BIPED study is a phase III study conducted in 12 sites across Canada, Australia and New Zealand. All participating hospitals are members of the Pediatric Emergency Research Canada (PERC) network [11] or the Paediatric Research in Emergency Departments International Collaboration (PREDICT) [12], both of which are affiliated with the Pediatric Emergency Research Networks (PERN). The BIPED study will define bronchiolitis as an episode of wheezing or crackles in an infant aged between 60 days and 12 months, alongside signs of an upper respiratory tract infection during the period deemed to be the season for RSV bronchiolitis. To reflect international clinical guidelines and practice, we have not restricted our definition of bronchiolitis to the first episode of wheezing or crackles and will enrol infants with second and subsequent episodes of bronchiolitis, with each infant only enrolled once into the study.

The active treatment in the BIPED study is two treatments of epinephrine (either via nebulisation (3 mg) or via metered dose inhaler and spacer (MDI-s) (625 mcg)) given 30 min apart in the ED and two doses of once daily oral dexamethasone (0.6 mg/kg per dose, up to a maximum of 10 mg), known as EpiDex. The first dose of dexamethasone will be given immediately before the first dose of epinephrine, and the second dose will be given 24 h later. The BIPED study will compare EpiDex to a placebo control (oral dexamethasone vehicle and nebulised normal saline or an inert placebo by MDI-s) by randomising participants in a 1:1 ratio. All study personnel, bedside clinicians, and participants/caregivers are blinded to the study group assignment. Participants will be followed up for 21 days following their ED enrolment visit, with the primary outcome collected at 7 days (168 h) post enrolment.

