### Sample size calculation

The sample size was determined using the average length criterion (ALC) [16], a Bayesian method for sample size determination. Using the ALC, we chose the smallest sample size for which the average length of the 95% high-density posterior credible interval for the difference in admission rates between placebo and EpiDex is below 9%. We determined the average length of the posterior credible interval across the prior-predictive distribution for the data [16]
. To determine the relevant prior distribution, we performed an expert elicitation for the probability of hospitalisation under placebo and EpiDex [17]. We simulated 1500 studies from the prior-predictive distribution and computed the posterior distribution for the absolute difference using 5000 simulations to estimate the average length of the 95% posterior credible intervals. Based on this simulation, the sample size of 410 participants per arm for the BIPED study was selected [17]. We allowed for a 5% loss to follow up, leading to a total target recruitment of 864 participants, 432 per arm.

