### Baseline characteristics

We will collect baseline information about the participants’ age, sex, weight, race, indigenous status and home environment, which includes the presence of smokers and attendance at daycare. We will also collect baseline clinical characteristics (respiratory distress assessment index (RDAI) [23], oxygen saturation, respiratory rate, heart rate, and temperature), the length of symptoms and treatments given prior to initial ED presentation, the medical history of the participant (such as breastfeeding, maternal smoking during pregnancy, prematurity, previous intubations, personal history of atopy [environmental allergy, food allergy and eczema, and previous significant/chronic illness], and previous episodes of wheezing/bronchiolitis) and family history of atopy (including asthma). Finally, if respiratory virus testing is available, the virus status will be reported.

Baseline characteristics will be compared across treatment groups and reported based on their data type. Specifically, categorical data will be summarised by numbers of participants within each category and percentages. If the continuous data are sufficiently normal, they will be summarised with the mean and standard deviation. Otherwise, the data will be summarised using the median and interquartile range. We will not undertake inferential statistics for baseline characteristics but will note the clinical importance of any imbalance.

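### Ten separately reported risk strata, with no treatment-by-risk term, are a weak way to find out whether the effect varies with risk

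*SAP article*

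**What the plan says.** The Heterogeneity of treatment effects analysis section describes a multivariable risk model that leaves out treatment assignment. The output is then specified: "We will create ten risk strata based on this model and report the median treatment effect with 95% credible intervals within each strata". The method named for these estimates is a Bayesian risk regression. The section gives no reason for ten strata. It states no interaction or trend between treatment and predicted risk, no pooling across strata, and no rule for declaring an effect in a stratum.

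The named predictors cover age, sex, prematurity, illness duration, earlier wheeze, eczema, family atopy and smoke exposure, and end with "breastfeeding and virus type". The list is framed as a floor, so others may be added. No measure of severity at presentation is named, although Baseline characteristics lists RDAI, oxygen saturation and respiratory rate among the data collected. The same section says of virus status: "if respiratory virus testing is available, the virus status will be reported".

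For size, Sample size calculation says "the sample size of 410 participants per arm for the BIPED study was selected". On attrition it adds "We allowed for a 5% loss to follow up", and it gives the result as "leading to a total target recruitment of 864 participants, 432 per arm". Allocation is by "randomising participants in a 1:1 ratio". Statistical principals gives an admission probability of 0.35 for the type 1 error simulation and a target difference of 8 points.

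**The concern.** The question behind a risk-based analysis is whether the treatment effect changes as baseline risk changes. The plan answers it with ten separate estimates and no quantity that compares them. Each estimate rests on about a tenth of a trial that was sized for one overall contrast. Some strata will look better and some worse by chance alone, and the plan has no stated summary to tell that scatter from a real gradient. The simpler subgroups under Subgroup analyses do get an interaction term with a 99% rule, so the ten-way split has less protection against chance patterns than the two-way splits.

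Two features of the risk model add to this. Severity at presentation is a natural candidate for predicting admission and is already collected, yet its inclusion is left open. Virus type is a named predictor, but a result exists only where testing was available, and the section does not say how an untested infant is scored. At stake is how informative and readable the heterogeneity report will be.

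**Working it through.** **The plan's own figure.** 410 / 0.95 = 431.6, so 432 per arm and 864 in total. This reproduces the stated target.

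**Stratum size.** 820 / 10 = 82 infants (41 per arm) if 410 per arm are evaluable; 864 / 10 = 86.4 (43.2 per arm) at full recruitment.

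**Assumptions.** No pooling across strata; flat priors; mean risk 31%, the midpoint of 0.35 and 0.27 (0.35 less the 8-point target). The article does not give the baseline risk behind its power figure, so 31% is an assumption, and 10% and 50% are shown as a range.

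**Precision per stratum.** Half-width = 1.96 × √(2p(1−p)/n), in percentage points:

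| Risk p | n = 43.2 per arm | n = 41 per arm |
|---|---|---|
| 10% | 12.7 | 13.0 |
| 31% | 19.5 | 20.0 |
| 50% | 21.1 | 21.6 |

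At 31% the full width is 39 to 40 points. The trial was sized so that the average interval length for "the difference in admission rates between placebo and EpiDex is below 9" percentage points, but that figure uses elicited priors and is not like for like. With flat priors at 0.35 v 0.27 the whole trial gives a full width of 12.3 points (432 per arm) to 12.6 (410 per arm). Ten strata multiply this by √10 = 3.16.

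**Point estimates in the wrong direction.** Take a uniform 8-point benefit and n = 43.2.
- SE = 0.195 / 1.96 = 0.0995.
- P(one stratum's estimate favours placebo) = P(Z > 0.08 / 0.0995) = P(Z > 0.804) = 0.21.
- Expected number among ten: 10 × 0.21 = about 2.
- P(at least one) = 1 − 0.79^10 = 0.91.

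Simulation with binomial counts gives a little less, 84 to 86%, because exact ties at zero are not counted as favouring placebo. With a common effect in all strata (0.35 v 0.27), the gap between the lowest and highest of the ten estimates has a median of 30 points (5th to 95th percentile 19 to 44).

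**Intervals wholly on the harm side.** Same inputs: P(one stratum) = P(Z > 1.96 + 0.804) = 0.0029, and P(at least one of ten) = 1 − (1 − 0.0029)^10 = 0.028, about 3%.

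**Strata against a trend.** Suppose the log relative risk varies by ±0.5 across the strata (an assumption). Two simulations found that a heterogeneity test on ten strata detects this in about 36 to 43% of trials, and a linear trend across the same strata in about 83 to 84%. The gain comes from using the ordering of the strata, with no extra data.

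**Fewer strata.** Quarters hold 102.5 to 108 infants per arm. At 31% risk, 1.96 × √(2 × 0.31 × 0.69 / 108) = 12.3 points (12.7 at 102.5). In simulation with a uniform effect, at least one quarter points the wrong way in about 31% of trials.

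**Virus type.** The share tested is not given. If 50 to 80% were tested (assumption) and the rest were dropped, a stratum would hold 864 × 0.5 / 10 = 43 to 864 × 0.8 / 10 = 69 infants. With 1.96 × √((0.35 × 0.65 + 0.27 × 0.73)/n) at n = 21.6 and 34.6 per arm, the half-width is about 27 and 22 points.

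**The case against.** - **Reading the strata as harm.** A reader might infer that the analysis will show harm in some strata even if the effect is uniform. The documents do not support that. The 84 to 91% concerns point estimates only; each is reported with its interval, and an interval wholly on the harm side would appear in only about 3% of such trials. The section declares nothing at stratum level. This objection stands: the output would be uninformative rather than misleading to a careful reader.
- **Pooling.** The section does not say that strata are analysed separately with flat priors. Shrinkage across strata would narrow the intervals. Analysis for the primary endpoint calls for minimally informative priors on coefficients other than the elicited treatment effect, which points towards flat priors here, and no pooling is stated. The half-widths therefore remain conditional on that reading.
- **Severity.** It is tempting to say that severity is excluded and that the strata will separate risk poorly. The predictor list is only a floor, so severity is allowed, and no discrimination figure is given for any version of the model. What remains is that the plan permits severity without committing to it.
- **Virus type.** It is also tempting to say that untested infants have no valid risk score, or that testing follows admission. An untested category would give them a score, and Handling of missing data has a rule for missing covariates, though it is framed around the primary analysis. Nothing in the article links testing to outcome. What remains is that the handling is not stated for this model.
- **Importance.** The analysis is supplementary and has no decision rule. Quarters still give half-widths wider than the 8-point target, so reducing the number of strata only lessens the noise. Both points stand, and they are why the continuous model is the substance of the fix.

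**Conclusion.** The point holds as one of method. Ten strata of about 41 to 43 infants per arm give risk-difference half-widths of about 20 points against a target of 8, and estimates that scatter over some 30 points when there is no heterogeneity at all. Without a treatment-by-risk term, the planned display is a weak way to detect an effect that changes with risk. The figures rest on no pooling, flat priors and about 31% mean risk; strong shrinkage would reduce them. The detection comparison rests on an assumed gradient.

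The two predictor points are smaller. They ask for commitments that the text leaves open and do not show that the risk model is wrong. The primary result and its interpretation are not affected.

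**What to change.** Before database lock:

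1. Make the main heterogeneity analysis one Bayesian model with treatment, predicted risk on the linear-predictor scale, and their interaction. Report absolute and relative effects with credible intervals along the risk scale. Allow a spline if linearity looks doubtful.
2. Keep strata for display only, preferably quarters, and state whether stratum estimates are pooled and with what priors.
3. Name RDAI, oxygen saturation and respiratory rate among the required predictors.
4. For virus type, use only results known before randomisation, with an explicit category for untested infants, or leave virus type out of the risk model.

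No new data are needed. The cost is SAP wording, a less granular display, and a linearity assumption that the spline can relax.

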### Trial status

The BIPED study was registered on June 25, 2018, and started recruitment in December 2018. Recruitment and follow-up were completed in January 2025. Final monitoring visits will be completed by April 2025. The study database will be cleaned and checked for completeness before the data are analysed. Following this process, the database will be locked, and the statistical analysis will be undertaken using the methods specified in this SAP. We anticipate data locking by the end of September 2025.

## Data Availability

No datasets were used to develop this article as analysis was not undertaken. Thus, this consideration is not applicable.

## Abbreviations

BIPED: Bronchiolitis in Infants Placebo Versus Dexamethasone Study
ED: Emergency department
SAP: Statistical analysis plan
RSV: Respiratory syncytial virus
PERC: Pediatric Emergency Research Canada
PREDICT: Paediatric Research in Emergency Departments International Collaboration
PERN: Pediatric Emergency Research Networks
MDI-s: Metered dose inhaler and spacer
EpiDex: A combination of inhaled epinephrine and dexamethasone
REB: Research Ethics Boards
DSMB: Data and safety monitoring board
DCC: Data coordination centre
WCHRI: Women and children’s Health Research Institute
REDCap: Research electronic data capture
ICU: Intensive care unit
CPAP: Continuous positive airway pressure
ALC: Average length criterion
CONSORT: Consolidated Standards of Reporting Trials
RDAI: Respiratory distress assessment index
MedRA: Medical dictionary for regulatory activities
